#### 6.2 Exploratory Analysis:

We will test a series of interaction terms to determine whether the effect of the intervention varies by subgroups. For example, it is possible the intervention may have different effects for women than men, or for heroin users compared to prescription opioid users. We also anticipate the intervention may have different effects depending on whether the patients are in a rural or urban area. To examine these subgroup differences, we will construct interaction terms that are the product of demographic variables and intervention condition (e.g., sex x condition, drug of choice x condition) and will repeat our outcomes analyses while including the interaction terms. If interaction terms are found to be statistically significant, we will stratify the sample and examine the intervention effect separately by subgroup.

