## Analysis Plan

- 6 We hypothesize that in the 9 months following their index overdose, patients exposed to the MROT will: H1: be more likely to initiate MAT (Primary outcome) H2: have fewer non-fatal ODs (Primary outcome) H3: be retained in MAT longer (Secondary outcome) H4: be less likely to die of a subsequent OD (Secondary outcome) All analyses will be conducted using the intent-to-treat principle. Demographic and descriptive statistics will be calculated at baseline and at 9-months following the index overdose. The baseline characteristics and main outcomes between the intervention and control groups will be compared using the chi-square test and the two-sample t-test. To test the hypotheses with the dichotomous outcome (initiation of MAT) and the ordinal outcome (incidence of non-fatal OD) we will use generalized linear mixed effects models (SAS PROC GLIMMIX) and Bayesian hierarchical models (SAS PROC MCMC) to account for the complexity of non-normal outcomes and intricate cluster effects due to the interdependence of patients within hospitals. The sensitivity analysis for Bayesian hierarchical models will also be performed. For the time to treatment, retention in treatment, and death due to subsequent OD outcomes, we will apply marginal Cox models (SAS PROC PHREG) to estimate the main effect of intervention exposure and use the robust sandwich covariance matrix estimation approach to account for the intracluster dependence. Individual demographic information including age, race, sex, drug of choice (heroin vs. prescription opioids), insurance type (e.g., Medicaid vs. private), and location of residence (urban vs. rural) will be included in the mixed effects models and marginal Cox models to control for potential confounding effects. We will obtain records from the SSA for 9 months prior to the index overdose for all participants, to allow us to control for prior history of non-fatal overdose and MAT utilization. Other covariates at the hospital level will include location (e.g., Northern Nevada vs. Southern Nevada, rural vs. urban) and hospital type (e.g., regional, university, trauma center, etc.). In addition to the statistical approach described above, we will also employ a propensity score (PS) matching approach as a secondary analysis. PS matching is particularly well-suited to "natural experiments" in which assignment to condition cannot be manipulated, such as the implementation of state programs. The approach involves calculating the probability of assignment to a treatment or exposure using logistic regression in which we enter observed characteristics that could influence assignment. In this case, known characteristics of patients such as age, sex, location of residence (rural vs. urban), previous history of overdose, or previous history of MAT enrollment. The PS reduces the large set of possible covariates that could influence selection into the intervention or control

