#### 6.1 Inference Criteria:

A p-value of  $<0.05$  will be considered statistically significant. 95% Confidence Intervals will be reported and all hypothesis testing will be two-sided. All analyses will be performed using SAS Version 9.4 for Windows.

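### Section 6.2 estimates subgroup effects only where an interaction reaches p<0.05, so the stratified effects are selected for large differences and modest real ones usually get no estimate

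*Protocol*

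**What the plan says.** Section 6.2 opens with "We will test a series of interaction terms to determine whether the effect of the intervention varies by subgroups". Sex and drug of choice are given as examples: "the intervention may have different effects for women than men, or for heroin users compared to prescription opioid users". Area is put more firmly: "We also anticipate the intervention may have different effects depending on whether the patients are in a rural or urban area". The investigators "will repeat our outcomes analyses while including the interaction terms", and then apply the gate: "If interaction terms are found to be statistically significant, we will stratify the sample and examine the intervention effect separately by subgroup".

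Section 6.1 states when a p-value "will be considered statistically significant" (below 0.05) and adds "95% Confidence Intervals will be reported and all hypothesis testing will be two-sided". It sets no separate criterion for exploratory tests, and the protocol mentions no multiplicity adjustment.

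The Measured Variables section names two primary outcomes (MAT initiation, non-fatal overdose) and two secondary outcomes (MAT retention, fatal overdose). The Analysis Plan adds a model for time to treatment. The Description section extends the outcomes evaluation to hospitals in rural and frontier Nevada.

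**The concern.** The rule makes a significance test the condition for estimating a subgroup effect. This has three consequences.

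- **Selection.** A stratified effect is looked at because the observed difference was large. When interaction power is low, such differences overstate the truth on average.
- **Missing estimates.** A real but modest difference usually fails the test, and then no subgroup-specific effect is planned. A non-significant interaction does not show that the effect is the same in both groups, and without subgroup intervals a reader cannot see what the data allow.
- **Loss of information.** Refitting in each stratum divides the patients, and the anticipated six intervention hospitals, across separate clustered models. One full-sample model with the interaction term gives the same contrasts without that loss.

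Whether the outreach teams work differently in rural areas matters for any decision to extend the programme. The protocol makes rural Nevada part of its purpose and expects that a difference is possible. A low-powered gate is a poor way to decide whether to look.

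**Working it through.** The protocol gives no number of interaction tests, interaction power or false-positive rate, so there is no stated figure to reproduce.

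**Inputs from the protocol**
- Sample sizes (section 4.2): 308 intervention and 521 control (829, called very conservative); 1232 and 2084 (3316, called reasonably anticipated).
- MAT initiation (section 4.1): 5% control, 33% intervention.
- Non-fatal overdose (section 4.1): 7-12% control, reduced by about 47%. The midpoint is 9.5%, giving 9.5% × 0.53 = 5.0% with intervention.
- Two-sided 0.05 (section 6.1).

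**Assumptions**
- Binary modifier split evenly, with the planned rates in both halves.
- Independent patients; clustering would change the figures.
- Non-fatal overdose treated as yes/no, although the Analysis Plan calls it ordinal.

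**1. Size of interaction needed to pass**

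In each half, var(log OR) = 1/a + 1/b + 1/c + 1/d, where a to d are the expected counts with and without the event in each arm. The interaction SE is the square root of the sum over the two halves, and the threshold is exp(1.96 × SE).

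MAT at 829, per half: control 260.5 × 0.05 = 13.0 events; intervention 154 × 0.33 = 50.8 events. Variance = 1/13.0 + 1/247.5 + 1/50.8 + 1/103.2 = 0.110. SE = √0.220 = 0.469.

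Overdose at 829, per half: control 24.7 events of 260.5; intervention about 7.75 of 154. Variance = 0.180. SE = √0.361 = 0.601.

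At 3316 both arms are four times larger, so each SE halves.

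**2. Chance that a true ratio of odds ratios of 1.5 passes**

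Φ(ln 1.5/SE − 1.96) + Φ(−ln 1.5/SE − 1.96), with ln 1.5 = 0.405.

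**3. Average size of those that pass when no interaction is real**

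The mean of |z| given |z| > 1.96 is 2.34, so the geometric mean ratio is exp(2.34 × SE).

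| | SE | Threshold | True 1.5 passes | Null average if passed |
|---|---|---|---|---|
| MAT, 829 | 0.469 | 2.5 | 14% | 3.0 |
| Overdose, 829 | 0.601 | 3.2 | 10% | 4.1 |
| MAT, 3316 | 0.235 | 1.6 | 41% | 1.7 |
| Overdose, 3316 | 0.300 | 1.8 | 27% | 2.0 |

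With control overdose rates of 7% or 12% in place of 9.5%, the overdose threshold is 3.9 or 2.9 at 829, and 2.0 or 1.7 at 3316. If one subgroup held only 20% of patients (an assumption, for example for rural), the thresholds would be 3.2 (MAT) and 4.4 (overdose) at 829, and 1.8 and 2.1 at 3316.

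**4. Chance of at least one false positive**

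Three named modifiers on four outcomes make 12 tests, or 15 with time to treatment. If the tests are independent and no interaction is real, the chance is 1 − 0.95^m:
- m = 12: 46.0%
- m = 15: 53.7%
- m = 6 (two primary outcomes only): 26.5%

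The outcomes come from the same patients, so independence is an upper reference. Simulated two-sided z-tests, with correlation 0 to 0.3 between modifiers, give:

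| Correlation between outcomes | 12 tests | 15 tests |
|---|---|---|
| 0.3 | 42-44% | 49-51% |
| 0.5 | 38-40% | 44-46% |
| 0.8 | 29-31% | 32-34% |

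If all six individual covariates in the Analysis Plan were used, each as a single term, 24 or 30 independent tests would give 71% or 79%.

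**The case against.** The strongest reply is that the section is labelled exploratory and worded tentatively, and that none of H1-H4 is a subgroup hypothesis. No primary or secondary conclusion depends on it, unadjusted testing there is normal, and the list of modifiers may be fixed in an analysis plan that is not shown. Testing the interaction before looking within strata is also a conventional guard against over-reading chance differences. All of this stands against a charge of missing multiplicity control. It does not remove the gate, which is a rule the protocol itself states; an analysis plan would have to contradict section 6.2 to drop it.

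Three stronger readings are tempting, and the documents do not support them.

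- A reader might infer that non-significant interactions go unreported. The text gates only the stratified analysis, and section 6.1 promises confidence intervals. Interaction estimates may well be shown throughout; what is conditional is the effect within each subgroup.
- A reader might take a false subgroup finding to be about a 50% event. That needs independent tests and no real interaction anywhere. Time to treatment also carries much the same information as MAT initiation, so 54% for 15 tests is high. The count itself is inferred from an open-ended list.
- A reader might take the 829-patient thresholds as the expected ones. At 3316, which the protocol regards as the reasonable expectation, they are much lower.

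**Conclusion.** The point holds as a cheap improvement to an exploratory section. The rule selects stratified effects for large differences and usually yields no subgroup estimate when a real difference is modest. The threshold ratio of odds ratios is about 2.5 (MAT initiation) and 3.2 (non-fatal overdose) at 829 patients, and 1.6 and 1.8 at 3316. Even at the larger size, a true ratio of 1.5 fails the gate more often than it passes. These figures rest on an even split, independent patients and the planned rates.

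The false-positive range of roughly 30% to 54% for the named terms (26% for the two primary outcomes under independence) is a reason for cautious wording, not a breach of any error rate that the protocol claims to control. The selection problem does not depend on that range.

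**What to change.** In section 6.2:

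1. Delete the rule that stratification follows a significant interaction.
2. For sex, drug of choice and rural/urban, fit one full-sample interaction model per outcome. From it, report the subgroup-specific intervention effects, the interaction estimate and the 95% intervals, whatever the p-value.
3. State that these results are exploratory and that the section 6.1 threshold supports no subgroup claim.

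This takes a few sentences in the protocol and one extra estimate statement per model. It needs no new data and leaves the primary analysis untouched. The downside is a longer table of mostly wide, inconclusive intervals, in which a single subgroup can be over-read; the third sentence and the interaction estimate beside each pair are there to limit that.
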